### Community Engagement Methods

Community-based participatory research methods will inform the study and cancer prevention campaign. Partnership processes aligned with the model by Sandoval et al [144] will provide a framework for the study: (1) knowledge of *contexts* that inform catchment area needs; (2) culturally informed *partnership processes* guiding engagement; (3) *intervention and research* protocols responsive to rural, low-income, and underserved conditions; and (4) participatory *outcomes* disseminated to partners. The research team will draw on the community networks of the Four Corners Cancer Centers Collaborative through each cancer center’s Community Outreach and Engagement program [145] to convene 2 community advisory boards for the project—an Emerging Adult Advisory Board (EAAB) and a Stakeholder Organization Advisory Board (SOAB). Up to 16 emerging adults from rural counties in the Four Corners states, diverse in gender and ethnicity, will be recruited to serve on the EAAB. The EAAB will meet quarterly with investigators in years 2 and 3 and biannually in years 1, 4, and 5. Members provide input on the social media campaign and implementation protocols (year 1) and review proposed posts (years 2 to 3), with attention to the relevance of posts for the circumstances experienced by rural emerging adults, especially the challenges experienced by low-income and marginalized emerging adults. Up to 4 stakeholder organizations that provide health promotion and cancer prevention services to rural emerging adults in each of the 4 states will be recruited for the SOAB. The SOAB will meet twice annually to review messaging, identify local resources, and plan dissemination efforts. Both advisory boards will advise on trial findings and dissemination efforts in years 4 to 5.

A series of focus groups with up to 8 rural emerging adults per group, meeting the inclusion and exclusion criteria (Textbox 1), will be conducted during the project to help develop the social media campaign. Discussions will cover cancer risk behaviors, social media use, health information seeking, misinformation, the context of health behaviors, and current issues and trends. Emerging adults will review social media posts and suggest how to engage rural emerging adults and reflect local contexts and issues. The results will be summarized and used to adapt posts to be responsive, timely, and engaging for emerging adults and targeted to key subgroups.

### Measures

#### Primary Outcomes: Cancer Risk Behavior Outcome Measures

We will use validated self-report measures of each cancer risk behavior in the T_0_-T_5_ surveys presented in Table 1.

**Table 1 table1:** Primary and secondary cancer risk behavior outcome measures.

Cancer risk behavior	Measure	Metric
Physical activity	Primary and secondary: Global Physical Activity Questionnaire [146]	Minutes per week of MVPA^a^ (primary) Meet 150 minutes per week goal (secondary)
Diet	Primary: Dietary Screener Questionnaire [147,148] Secondary: other meal behaviors [149-152]	Intake per day of fruits, vegetables, whole grains or fiber, added sugars (from sugar-sweetened beverages), and red or processed meats Frequency of eating meals and snacks, fast food, and skipping meals
Nicotine product use	Primary: 30-day prolonged tobacco or nicotine product abstinence [153] Secondary: 7-day point prevalence of smoking [153] Secondary: readiness to quit [154]	Use in the past 30 days (every day, some days, and not at all) Use in the past 7 days (every day, some days, and not at all) 10-point rating (1=no thought of quitting and 10=taking action to quit)
Alcohol intake	Primary: consumption of alcoholic drinks [155] Secondary: binge drinking (male individuals: 5 drinks per sitting and female individuals: 3 drinks per sitting)	Number of days in the past 30 days; number of drinks per occasion Number of times in the past 30 days
UV exposure	Primary: sunburn prevalence [156] Secondary: sun protection behavior [157]	Number of sunburns Percentage of sun exposure days using sun protection
HPV^b^ vaccination	Primary: any dose of HPV vaccine [158] Secondary: completion of vaccine series	Received 1 or more doses Received 2 or 3 doses as recommended for age

^a^MVPA: moderate to vigorous physical activity.

^b^HPV: human papillomavirus.

Self-report measures are most practical for this pragmatic trial, with the large sample of emerging adults in 4 geographically large states (approximately 1,100,700 sq km), web-based recruitment, and a multirisk factor approach that makes clinical and observational measures infeasible. The recall period for nicotine abstinence, alcohol use, and sunburn prevalence measures will be 30 days, which improves reliability [156]. Physical activity and other meal behaviors will be measured for the past 7 days, and HPV vaccination will be measured from baseline.

The primary outcome measures of physical activity, diet, and nicotine abstinence will be validated in subsamples of emerging adult participants at baseline and at the 52-week posttest stage. Physical activity and diet self-report measures will be verified with (1) accelerometry (ActiGraph GT9X) [159,160] and (2) 24-hour recalls (for 3 random days; 2 weekdays and 1 weekend day) [161] in a subsample of emerging adults (139/1000, 13.9%) at baseline and repeated at 52 weeks. Nicotine abstinence self-report measures will be verified via saliva cotinine assays (Salimetrics assay) on a subsample of 15% emerging adults reporting abstinence at 52 weeks [153]. Objective measurement of alcohol use, sunburn, and HPV vaccination is infeasible within the scope of the trial.

#### Mediators

Mediators will be assessed in all surveys. These include theoretical antecedents—cancer risk (SCT; severity and susceptibility: 6 items); self-efficacy and response efficacy (SCT) [162]; cost of cancer prevention [162]; descriptive norms (SCT; 2 items; prevalence among people you know and 5 people you know best) [163]; social support from family, friends, and partners (SCT); relatedness (SDT; 4 items) [164]; autonomy and motivation (SDT; 10-point contemplation ladder) [154,165]—family and friend communication about cancer prevention (SDT and DIT; if emerging adults shared information from feed with family and friends) [166]; and vaccine antecedents (ie, confidence, constraints, complacency, calculation, and collective responsibility [167]). Digital and media literacy will be assessed with 3 competency measures—self-perceived media literacy (4 items) [168], perceived social media literacy (6 items) [169], and eHealth literacy (8 items) [170]—along with cancer prevention misinformation (8 accurate and 8 inaccurate Likert statements recoded for belief in misinformation).

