The effect of the treatment on each of the primary outcomes will be examined using a linear mixed-effects model for a stepped-wedge design, as outlined by Hussey and Hughes [183] and Li et al [184]. Repeated measures (6 per individual—T_0_, T_1_, T_2_, T_3_, T_4_, and T_5_ in Figure 1) will be regressed on time since the start of the study (“calendar time”) and time since the start of message exposure (“exposure time”), both of which are expressed as categorical variables via dummy codes. Any mediators found to be significantly impacted by the treatment will be subsequently examined as mediators of the treatment effect on the outcomes via formal mediation models. Multilevel mediation models will be fit as described by Preacher [185] using the structural equation modeling program. As moderation tests require a vastly larger sample than tests of main effects [186], we will examine them without conducting null hypothesis significance tests [187]. We will estimate each model, evaluate the effect magnitude as a function of the moderator, construct bootstrap CIs to illustrate uncertainty, and use false discovery rate controls [182,187]. Linear mixed-effects models for hypothesis 1 will be extended to consider effect modification because of cancer risk behaviors, campaign exposure variables, biological sex, and the time of year of data collection (to control for seasonal fluctuations in UV levels, food availability, and alcohol intake).

Finally, behavioral and experiential engagement will be tested for campaign dose response (ie, duration of the campaign) related to cancer risk behaviors. In addition, behavioral engagement with posts (ie, views, reactions, and comments) on certain topics (eg, risk behaviors, media literacy, or family communication) and formats (eg, text, video, or interactive features such as polls) will be examined to determine if they have an impact on campaign effectiveness.

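### The 10-point ladder appears as both a secondary nicotine outcome and a mediator, and nothing keeps it out of the nicotine mediation models, so some apparent mediation can come from the outcome itself.

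*Protocol article*

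**What the plan says.** All references are to the protocol article.

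- **Outcome role.** Table 1, in the section on primary outcome measures, lists "Secondary: readiness to quit [154" for nicotine, scored as a "10-point rating (1=no thought of quitting and 10=taking action to quit". The primary nicotine outcome in the same row is "Primary: 30-day prolonged tobacco or nicotine product abstinence [153", and the text below the table gives nicotine abstinence a 30-day recall period.
- **Mediator role.** The Mediators section includes "autonomy and motivation (SDT; 10-point contemplation ladder) [154,165". Reference 154 and the 10-point length match the readiness outcome.
- **Timing.** "Mediators will be assessed in all surveys". The outcomes are collected in the T0 to T5 surveys, so both come from the same questionnaires.
- **Rule that brings them together.** Hypothesis Testing states: "Any mediators found to be significantly impacted by the treatment will be subsequently examined as mediators of the treatment effect on the outcomes". It makes no exception for a mediator that also serves as an outcome.

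**The concern.** A mediator should lie between the intervention and the outcome, and should not be a record of the outcome. Two features of this plan put that in doubt for nicotine.

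First, someone who has stopped using nicotine has acted on quitting and may mark the top of the ladder for that reason. The abstinence question looks back over 30 days, while the ladder describes the respondent when answering. If the two are paired within a survey, the outcome window comes before the supposed mediator. A campaign that changed abstinence by any route could then shift the ladder. The screening rule would admit the ladder as treatment-affected, and the model would credit it with part of the effect.

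Second, if readiness to quit is itself modelled as an outcome and the item is the same, mediator and outcome are one score and the analysis is circular.

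At stake is the mechanism statement for nicotine. The trial could report that motivation carried part of the campaign's effect on abstinence when that part reflects how abstainers answer the ladder.

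**Working it through.** The article gives no mediated share, ladder distribution or ladder-abstinence correlation, so there is no stated figure to reproduce. The check asks how much mediation the overlap alone could create.

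**Inputs**
- Abstinence 0.40 without and 0.48 with the campaign, so the total effect is c = 0.08. These are the Power Analysis section's generic rates for a binary outcome, not nicotine rates.
- Assumed: motivation has no causal effect on abstinence, so true mediation is zero.
- Assumed: a share q of abstainers mark 10 because they have already acted. All other ladder scores are independent of arm and abstinence.
- Assumed ladder for everyone else: uniform on 1 to 9 (mean 5, variance 60/9 = 6.667). The alternative is a rounded normal with mean 5 and SD 2.5, limited to 1 to 10.
- Mediator and outcome are taken from the same survey.

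**Formulas (uniform case)**
- Mean ladder difference, abstainers minus users: δ = (10 − 5)q = 5q.
- Path a (campaign to ladder): a = cδ = 0.08 × 5q = 0.4q.
- Average within-arm variance of abstinence: (0.40 × 0.60 + 0.48 × 0.52)/2 = (0.2400 + 0.2496)/2 = 0.2448.
- Within-arm ladder variance, with 56% users and 44% abstainers on average: V = 0.56 × 6.667 + 0.44 × [(1 − q) × 6.667 + 25q(1 − q)] + 0.2448δ².
- Path b (ladder to abstinence, given arm): b = 0.2448δ/V.
- Apparent mediated share: ab/c = 0.2448δ²/V.

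**Example, q = 0.5.** δ = 2.5 and a = 0.20. V = 3.733 + 0.44 × (3.333 + 6.25) + 0.2448 × 6.25 = 3.733 + 4.217 + 1.530 = 9.480. Then b = 0.612/9.480 = 0.0646, and the share is 0.20 × 0.0646/0.08 = 16%.

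**Example, q = 1.** δ = 5 and a = 0.40. V = 3.733 + 0.2448 × 25 = 9.853. Then b = 1.224/9.853 = 0.1242, and the share is 0.40 × 0.1242/0.08 = 62%.

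A simulation of 2,000,000 records per setting agrees:

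| Share of abstainers marking 10 | Formula, uniform | Simulated, uniform | Simulated, rounded normal |
|---|---|---|---|
| 0 | 0% | 0% | 0% |
| 0.10 | 0.8% | 0.8% | 0.8% |
| 0.25 | 4.6% | 4.5% | 5.1% |
| 0.50 | 16.1% | 16.3% | 16.9% |
| 0.75 | 34.5% | 34.6% | 37.6% |
| 1.00 | 62.1% | 62.5% | 66.1% |

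**Would the ladder pass the screen?** A rough scaling from the plan's own power statement (0.80 at a standardised difference of 0.2, 115 per cohort, alpha .008) gives an expected z of 2.652 + 0.842 = 3.494. At q = 1 the shift is 0.40/√9.853 = 0.127 SD. With 175 per cohort, the expected z is 3.494 × (0.127/0.2) × √(175/115) = 2.75, and the chance of passing is Φ(2.75 − 2.652), or about 54%. At q = 0.5 the shift is 0.20/√9.480 = 0.065 SD, the expected z is 1.40, and the chance is about 10%. This assumes that .008 also applies to mediators, which the article does not say. At .05 the two figures would be about 78% and 29%.

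**The case against.** The strongest reply has six parts.

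- **Same instrument?** This is inferred from the shared reference and length. The Mediators entry also cites reference 165, gives no anchors, and does not say whether the ladder is nicotine-specific or adapted to each behaviour. That stands: identity is the natural reading but is not stated.
- **Is the top rung the outcome?** A reader might infer that rung 10 is abstinence itself, so that mediation is largely built in. The documents do not support this. The anchor is about acting to quit, and a current user who is trying to stop can mark 10. The largest shares need nearly every abstainer to mark 10. Enrolment is not limited to nicotine users, so abstainers include never-users with nothing to quit.
- **The screen.** A reader might also infer that the plan would report false mediation. The scaling above shows that the ladder could well fail the screen, so it could do so, no more.
- **Same-visit pairing.** The article does not state it, and a fuller plan might lag the mediators. That stands, but lagging alone would not settle the ladder's two roles.
- **Circularity.** The paragraph containing the mediation rule opens with the primary outcomes, so readiness to quit may never be modelled there. The circular case is conditional.
- **Importance.** Hypothesis 2's list of mediators omits motivation and autonomy. However, the section on the theoretical approach names both as theoretical mediators, and the Mediators section lists their measure.

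None of this removes the double listing or the absence of an exception in the rule.

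**Conclusion.** The concern holds in limited form. One ladder appears in two roles, and the stated rule allows it into mediation models of nicotine outcomes. With no true mediation, the overlap could yield an apparent share anywhere from 0% to about 66%. Where it falls depends on the proportion of abstainers who mark 10, which the article does not give. The range rests on the generic rates of 0.40 and 0.48, same-survey pairing, the two assumed ladder distributions, and the other abstainers answering as users do. It is an illustration of what could happen, not an estimate of bias in this trial.

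The reach is one candidate mediator for one of six behaviours. The Hypothesis 1 tests, the alpha of .008 and the sample size are unaffected. The change is worth making because the double role is visible in the text and the correction costs almost nothing.

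**What to change.** Keep readiness to quit as a secondary outcome. State in the Mediators and Hypothesis Testing sections that the nicotine ladder is not a mediator in any model of a nicotine outcome.

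If motivation is still to be examined for nicotine, use the ladder score from the preceding visit in the full randomised sample, adjust for baseline nicotine use, and report the result as exploratory. Do not restrict this to people still using nicotine after randomisation. That would condition on a state the campaign may have changed, and it would sit badly with the plan's intent-to-treat commitment.

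The cost is a few sentences, one fewer same-visit mediator for nicotine and, if the lagged score is used, some precision. No new data are needed, because the six survey waves already supply the earlier scores.

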### Objectives

Our proposed intervention will aim to aid rural emerging adults in making informed decisions to reduce cancer risks related to infrequent physical activity, unhealthy diet, alcohol intake (per 2020 American Cancer Society guidelines [6]), nicotine product use, UV exposure, and lack of HPV vaccination uptake. In addition, it will help them critically evaluate and resist misinformation and marketing that promote cancer and other health risk behaviors and support emerging adults to be media literate when using digital media. The trial will test the following hypotheses:

Hypothesis 1: emerging adults will increase MVPA and healthy eating patterns, reduce nicotine product and alcohol use and sunburns, and increase HPV vaccine uptake from baseline to final assessment when receiving the social media intervention.Hypothesis 2: the positive impact of the social media campaign on cancer risk factors among emerging adults will be mediated by improved cancer risk knowledge and beliefs (ie, self-efficacy and response efficacy, norms, social support, and vaccine antecedents), digital and media literacy skills, misinformation identification, and family communication.

Analyses will also explore whether the impact of the campaign differs according to (1) the level of emerging adults’ engagement with it, (2) cancer risk factors, and (3) the biological sex of the participants. The prospective randomized quasi-experimental design and its large sample will provide a rigorous evaluation of the social media campaign compared with many previous studies on social media that have used less rigorous nonrandomized controlled trial designs and small samples [81-86].

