#### Implementation of Social Media Campaign

The social media campaign will be implemented through Facebook private groups. A staff person will serve as the community manager and schedule posts twice a day on all 7 days of the week (1 message in the morning and 1 in the afternoon) to achieve reach [142,143]. In each cohort, emerging adults will receive welcome posts on purpose and ground rules (eg, respect for others) and then receive the ongoing feed delivered in their separate private group so that posts are identical across cohorts, timely, linked to current events and news stories, relevant for seasons, and engaging. We will not start each cohort at the beginning of the feed because it would require adjusting earlier posts to be current, making them dissimilar across cohorts. The community manager will monitor reactions and comments from emerging adults, answer questions, address uncertainty, and correct misinformation [58,124,133]. The community manager will promote peer influence by, for example, (1) recruiting high-frequency emerging adult users to be guest moderators for up to 3 days to schedule posts and reply to comments and (2) hosting Facebook Live events with emerging adult experts (eg, an emerging adult dietitian). If any bullying arises, the community manager will de-escalate it by (1) highlighting empathy and (2) sending direct messages to stop it. If participants leave a group, they will be contacted to see why. Project staff, except the community manager and the project coordinator, will be blinded to the cohort membership.

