Facebook’s private group function possesses unique features not found in other social media platforms. These distinctive qualities offer practical methodological advantages and enhance experimental rigor. Facebook remains one of the most popular social media platforms for emerging adults, used by 70% of the population nationally (among which 70% use it daily), with the majority reporting use in nearly all demographic groups, including by age, rurality, race, ethnicity, and income [43]. Thus, nearly all emerging adults will have existing accounts and be familiar with its interface. Other social media place limits on content delivery that would restrict cancer prevention messaging, including by restricting format (eg, YouTube and Instagram mainly use video and images), length (Snapchat and TikTok deliver short videos), and permanence (Snapchat posts last for 24 hours after posting), and they all restrict the ability to link to other web content more than Facebook. Facebook’s private group function will also help ensure that posts appear in users’ feed and will limit access to posts to group members (posts cannot be shared on other social media) to avoid contamination. Finally, Facebook has superior data analytics for tracking exposure to content compared with other platforms.

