#### Social Media Campaign Engagement Measures

Behavioral and experiential measures of campaign engagement [174,175] will be collected, guided by the model of engagement by Perski et al [176]. Behavioral measures will be (1) staff records of posts; (2) counts of emerging adults’ views, reactions (eg, like or sad), and comments extracted in identified format using our custom-written app and coded for content and pro, anti, or neutral sentiment by 2 trained research assistants [113]; and (3) use of resources on the project website recorded by the web server. Experiential measures will be collected in each postintervention test, including time spent and frequency of reading posts, flow experience (ie, social interaction, enjoyment, and concentration) [177], cancer information overload [178], and sharing post content with others.

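### Family communication, a hypothesis 2 mediator, is measured as sharing from the campaign feed, so its treatment effect is either guaranteed by definition or not estimable

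*Protocol article*

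**What the plan says.** All references are to the protocol article.

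- **Objectives.** The mediators named in hypothesis 2 include "digital and media literacy skills, misinformation identification, and family communication".
- **Mediators.** The construct is labelled "family and friend communication about cancer prevention". The parenthesis that follows gives the measure: "if emerging adults shared information from feed with family and friends". The section opens with "Mediators will be assessed in all surveys", which covers T0 and the waves before later cohorts begin.
- **Implementation of Social Media Campaign.** The feed is the campaign's own: participants "receive the ongoing feed delivered in their separate private group". The private-group function "will limit access to posts to group members (posts cannot be shared on other social media) to avoid contamination".
- **Randomized Stepped-Wedge Trial Design.** Cohorts start at weeks 1, 13, 26 and 39, and the time before a cohort starts is its control condition.
- **Hypothesis Testing.** The route into the mediation models is: "Any mediators found to be significantly impacted by the treatment will be subsequently examined as mediators of the treatment effect".
- **Social Media Campaign Engagement Measures.** The experiential measures, collected only at post-intervention tests, include "sharing post content with others".

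**The concern.** A mediator is useful when it could move with or without treatment, so that the randomized contrast shows whether treatment moved it. This item cannot. Someone whose cohort has not started has nothing from the feed to pass on, however much they talk at home about diet, alcohol or vaccination. The unexposed value is fixed by the wording of the question and not by behavior.

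The label names a broader construct than the item captures. The campaign content described under Social Media Posts likewise aims at conversation about prevention, with post content as only one part of it. If family conversation did not change at all but some participants forwarded posts, the plan would report a treatment effect on family communication and carry it into a formal mediation model.

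At stake is the interpretation of one named hypothesis 2 mediator.

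**Working it through.** **1. Unexposed cells.** Inputs are the start weeks (1, 13, 26, 39) and the survey weeks in the design section (T0 baseline, then 13, 26, 39, 52, 104). A survey that falls in a cohort's start week is taken as pre-exposure. This fits the article's statement that cohorts 2, 3 and 4 each have several baseline measures.

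| | T0 | T1 | T2 | T3 | T4 | T5 |
|---|---|---|---|---|---|---|
| Cohort 1 | 0 | 1 | 1 | 1 | 1 | 1 |
| Cohort 2 | 0 | 0 | 1 | 1 | 1 | 1 |
| Cohort 3 | 0 | 0 | 0 | 1 | 1 | 1 |
| Cohort 4 | 0 | 0 | 0 | 0 | 1 | 1 |

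Unexposed: 4 + 3 + 2 + 1 = 10 of 4 × 6 = 24. Exposed: 14. The 10 cells are all the control observations.

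**2. What the item yields there.** The article does not say how the question is put or scored before exposure. There are two possibilities.

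- *Scored as not shared.* The mediator is 0 with no variance in all 10 cells. The treatment effect on it equals the sharing rate among the exposed: p − 0 = p.
- *Skipped or not applicable.* The mediator is missing in all 10 cells and is observed only under exposure. Contrasts between exposure durations remain, but no contrast with control does. Full information maximum likelihood has no unexposed value to work from.

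Under neither reading does the screening rule show whether family communication changed.

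**3. How far this reaches into the mediation result.** The plan gives no figure to reproduce, so this was simulated for the first reading.

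- From the article: 175 completers per cohort, within-person correlation 0.5, α = .008, T0 to T5.
- Assumed: a two-sided test; sharing among the exposed of 10%, 30% or 50%; one exposed/unexposed indicator in place of the plan's dummy-coded exposure time; all 14 post-start cells treated as exposed, including T5.
- Models, with person and calendar-time effects: mediator on exposure; outcome on mediator and exposure. Mediation is declared if both paths are significant.
- 300 runs per scenario. The Monte Carlo standard error at a true rate of 0.8% is √(0.008 × 0.992 / 300) ≈ 0.5 percentage points.
- The confounded scenarios assume that more engaged users share more and also change more, by 0.2 SD of outcome per SD of engagement.

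In the two mediation columns the true mediator-to-outcome effect is zero. The paired figures are for a direct campaign effect of 0 and of 0.2.

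| Sharing | Treatment-to-mediator estimate | That path significant | Mediation declared, no confounding | Mediation declared, confounded |
|---|---|---|---|---|
| 10% | 0.10 | 100% | 0.3%, 0.3% | 39.7%, 44.3% |
| 30% | 0.30 | 100% | 1.0%, 1.0% | 70.0%, 69.7% |
| 50% | 0.50 | 100% | 0.3%, 1.7% | 79.0%, 78.7% |

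The first path is significant in every run, including those where the campaign changes no behavior, and its estimate is just the sharing rate. The second path is not fixed. Without confounding, false mediation stays at about the nominal 0.8%. With a true mediator effect of 0.2, mediation is declared in 85.7%, 99.0% and 99.7% of runs. Under the assumed confounding the mediator-to-outcome estimate is about 0.12 to 0.14 when the truth is zero.

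**The case against.** **Sharing campaign content is a legitimate mechanism.** The article ties this mediator partly to diffusion of innovations theory, and posts are meant to prompt sharing of their content. A mediator that is zero without treatment is not invalid in itself, and whether diffusion of campaign content carries the effect is a coherent question. This stands. It does not rescue the present plan, because the label is the general construct, the item is scheduled at all surveys, and the screening rule is uninformative for such a mediator.

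**The source is condensed.** The evidence is a short parenthesis in an article, the instrument is not shown, and a general item may exist. That limits certainty about the final questionnaire. It does not remove the point, which is about a stated definition that does not fit the article's own schedule and label. The conversations item under Potential Covariates does not fill the gap, since it concerns sources of cancer information and is measured at baseline.

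**Confounding affects every non-randomized mediator.** True, and the 40% to 79% range rests on a confounding strength the article does not give. What is particular here is that the item is close to a measure of engagement, and the plan itself expects engagement to relate to the risk behaviors.

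Three stronger readings are tempting, and the documents do not support them:

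- *That the whole mediation result is built in.* Only the treatment-to-mediator path is.
- *That hypothesis 2 cannot be answered at all for this mediator.* The mediator-to-outcome path is still estimated in exposed person-time, and without confounding it behaves properly.
- *That one item serves as both dose and mediator.* The engagement measure refers to others generally and is collected only after intervention; the mediator refers to family and friends and is set for all surveys. The wording overlaps, but identity is an inference.

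**Conclusion.** The point holds in a limited form. As described, the item is zero by definition or unanswerable in all 10 control cells of 24. The treatment effect on this mediator is therefore guaranteed (given any appreciable sharing; 10% was the lowest rate examined) or not estimable, and passing the screening step carries no information. Any indirect effect rests on comparing sharers with non-sharers during exposed time, which is not randomized, overlaps with an engagement measure and is open to confounding by engagement.

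The cell count assumes that start-week surveys precede exposure. The simulated rates depend on the assumed sharing rates and confounding strength and illustrate the mechanism; they do not predict this trial's error rate. T5 falls 52 weeks after the campaign ends (104 − 52), so what the item captures there depends on a recall period that the Mediators section does not give.

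The scope is one named mediator. The other mediators, hypothesis 1, the primary outcomes and the power calculation are unaffected.

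**What to change.** Measure the mediator with a source-neutral item: how often the participant talked with family or friends about cancer prevention in a fixed recall period, whatever the source, in identical words at T0 to T5. Use that item in the screening step and in the mediation models. Keep sharing of feed content as an engagement measure only, collected after exposure, and leave it out of the mediation models.

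The cost is one or a few reworded or added survey items, with negligible burden on respondents. The Project Initiation and Administration section reports that the measures are still being piloted, so the change can be made before launch. The source-neutral item will also pick up conversations unrelated to the campaign, so its treatment effect will be smaller than the sharing rate, but it will be a tested effect.
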